## Welcome

*Welcome to the Lindenwood University IRB Application. This application will guide you through the process of submitting your proposed research involving human subjects to the IRB ([Institutional Review Board](#)) for review.*

This application is an opportunity to consider the ethical dimensions of your research, while also allowing you to consider a few of practical aspects of your research protocol in more detail. We looking forward to partnering with you in this process of considering the rights, welfare, and dignity of all participants in the research process.

--

As you can see from the tabs along the left hand side, this application is set up to track with you through the life-cycle of a research protocol. Each tab addresses a new component or stage of the research process. Each tab also will connect you with a different ethical criterion used by the IRB to review your proposal.

**Each tab represents a different ethical step in considering the implications of your research for participants and others. Please keep the following general concepts in mind as you complete the application:**

- Are all risks to subjects minimized?
  - Are all risks reasonable in relation to the potential benefit?
  - Are all subjects selected with equity and respect?
  - Will you talk to subjects and obtain their consent?
  - Will you document the consent process?
  - Will you monitor the safety of subjects?
  - Will you protect the privacy of all subjects?
  - Are there any special ethical considerations for vulnerable populations?
-

\*required

**Do you or any of your Research Team Members have a Conflict of Interest related to this research?**

---

6.

*Please refer to the additional information in the "?" button for information about what constitutes a Conflict of Interest. The review of Conflicts of Interest by the Investigator Conflict of Interest Committee will occur in a process ancillary to the IRB application, to ensure the confidentiality of PI interests.*

✓ No

Yes

\*required

**Where will your research take place?**

---

7.

*List all research sites and locations. You should list any specific location, such as a school, institution, or a specific classroom. An online, gaming, or virtual "space" counts as a research location and should be listed. If you are collecting secondary data from a database, please list the database or source.*

Within the Exercise and Performance Nutrition Laboratory (EPNL) at Lindenwood University and Field House 110. Both of these sites are located within the same building (The Field House) and are approximately 15 seconds apart from one-another.

\*required

**Are any of these sites outside the United States?**

---

8.

*Please only answer "Yes" if your research will physically be conducted outside the United States, or data will be collected from sources outside the United States. Online surveying, social media, or similar virtual research spaces are not applicable to this question.*

✓ No

Yes

\*required

**Do any of these sites require permission or advanced notice?**

---

9. *Schools, organizations, business, and similar environments often require permission prior to conducting research in their facilities. Researchers at Lindenwood University are required to ensure compliance with these local policies prior to conducting research. If a research site is subject to HIPAA, FERPA, or other applicable regulations for the collection of research data, the site authorization must provide affirmation of adherence to these regulations at each site.*

☒ No

Yes

\*required

10. **Will any research be conducted at sites external to Lindenwood University that have their own IRB?**
- 

☒ No

Yes

\*required

11. **Are you requesting the Lindenwood University IRB to rely on another IRB for Single IRB (SIRB) Review?**
- 

☒ No

Yes

## Your Funding Information

\*required

**Will this research be supported by any funding?**

12.

*Please visit the [LU Grants and Sponsored Projects](#) website for more information.*

No

☒ Yes

\*required

**12a. Did you complete the [Pre-Award Proposal Review Process](#)?**

☒ Yes

No

\*required

**Please select your Sponsor.**

12b.

*Please select "Unknown" if you do not see your Sponsor Code. The IRB will assist in creating a new Sponsor Code for your funding agency.*

Name

-

- [Name - A to Z](#)
- [Name - Z to A](#)

Ingenious Ingredients, L.P.

\*required

12c. **What is the name of the PI who is the prime awardee of the funding?**

---

[name]

\*required

12d. **What is the nature of the funding?**

---

☒ Direct

☐ Indirect/Pass-Through

☐ Subaward

☐ Continuation/Renewal

\*required

**What is the Grant Title?**

---

A Pilot Study To Examine Changes in Resistance Training Adaptations After Leucine and Dileucine Ingestion

\*required

12f. **What is the Project Period for the Funding?**

---

Approximately December 2020 - August 2020

\*required

### What is your research question?

---

13. *Think of this section as your research "elevator pitch." Please briefly describe the question(s) or issues you are addressing with your research (limited to 100 words). You will be able to provide information on specific outcomes, hypothesis, or related analysis in a following question.*

This study seeks to compare the observed changes in resistance training adaptations after supplementation of isomolar (same volume of solution) amounts of leucine or dileucine in healthy resistance-trained men. This will provide a better understanding of supplementation with leucine versus dileucine over a 10-week period in regards to increasing muscular performance.

\*required

### How will you answer your research question?

---

14. *Please provide a brief summary of procedures you will use to collect or produce data (limited to 100 words). You will be able to provide more detailed protocol information in a following question.*

The study will be conducted using a randomized, double-blind approach with individuals being provided daily 2-gram doses of leucine, 2-gram doses of dileucine, or a placebo. Daily blinded supplementation will occur each day for a 10-week period of time while completing a heavy resistance training program. Participants follow the resistance training program for a total of 10 weeks. To assess the efficacy of the two different forms of amino acid supplementation on resistance training adaptations, changes in fat-free, lean, and fat mass will be determined using a 4-compartment body composition model. Skeletal muscle cross-sectional area will be assessed using ultrasound. Maximal strength, muscular endurance, and power will also be assessed. Participants will be required to provide weekly compliance and complete one supervised workout per week. After 2, 6, and 10 weeks of following the supplementation and resistance training regimens, participants will return to the laboratory to complete testing bouts consisting of identical assessments of body composition, muscular strength, muscular endurance, lower-body power, and anaerobic capacity. Adverse events related to each supplementation group will be recorded and assessed.

\*required

### What do you think are the most critical ethical issues with your research?

---

15. *Please provide one or two sentences describing what you think are the key ethical issues or concerns associated with your research. For example, your research poses significant risks to subjects, it may be difficult to obtain voluntary consent from participants, or you would like to interact with subjects who are vulnerable or often subject to coercion.*

Risks to subjects are reasonable in relation to anticipated benefits, if any, to subjects, and the importance of the knowledge that may reasonably be expected to result.

\*required

### Why is your research important, and how might your research findings contribute to scholarship or current study in your field?

---

*Please limit your response to 250 words. This response can include a summary or history of research in your question, issue, or area. You may attach 1-2 pages of bibliography or additional information as applicable.*

16. For the past decade, exceptional interest has been generated regarding the impact of the essential amino acid, leucine. Currently, it is well accepted that leucine operates as a key stimulator of protein synthesis in both animal and human research models. Further research has gone on to indicate that a minimum threshold of leucine exists within skeletal muscle before widespread activation of translational machinery occurs. In this respect, leucine doses of 1.7 – 3.8 grams have been reported to be the optimal range of leucine to activate muscle protein synthesis (Tipton, Ferrando et al. 1999, Paddon-Jones, Sheffield-Moore et al. 2004, Norton 2009). Different protein sources are widely known to have varying amounts of leucine, the branched-chain amino acids and the other essential amino acids (Phillips, Tang et al. 2009, Joy, Lowery et al. 2013). Dileucine is a unique peptide that consists of two leucine molecules bonded together. Currently, no published literature is available that has reported on the resistance training adaptations after supplementing with 2 grams of leucine or dileucine for a period of 10 weeks. These data are important for multiple reasons. For starters, studies have linked changes in leucine concentration with the anabolic potential of a given source of amino acids (Norton 2009). Furthermore, the speed as well as the magnitude of changes in leucine concentration may operate as key variables that explain the anabolic potential of dileucine.

**Attach additional information:**

16a.

[REFERENCES.docx](#)

\*required

## How will you measure your results or analyze your research data?

---

*Please include a list of your hypotheses, study aims, and/or intended study outcomes. Also include a brief description of any statistical analyses you may use to meet these outcomes. It is important to be clear about any intended outcomes, as this information is vital in assessing the prospective benefit of a research proposal.*

### **Specific Aims:**

1) In comparison to daily leucine supplementation, we aim to examine the impact of dileucine on the observed changes in strength, power, and body composition after eight weeks of supplementation and heavy resistance training.

2) In comparison to placebo supplementation, we aim to examine the impact of leucine and dileucine on the observed changes in strength, power, and body composition after eight weeks of supplementation and heavy resistance training.

### **Independent Variable**

Supplementation Status:

- 2 grams Dileucine (n=12)
- 2 grams Leucine (n=12)
- Placebo (n=12)

### **Dependent Variables**

Primary Endpoints:

- Fat-free mass
- Leg press 1RM
- Bench press 1RM
- Maximal isometric mid-thigh pull force production

17.

Secondary Endpoints:

- Fat mass
- Lean mass (DEXA)
- % Body Fat (DEXA)
- Total, extracellular, and intracellular body water
- Skeletal muscle cross-sectional area via ultrasound
- Bench press repetitions to fatigue
- Leg press repetitions to fatigue
- Peak anaerobic power
- Mean anaerobic power
- Rate of fatigue
- Maximal concentric rate of force development

**STATISTICAL ANALYSIS:**

All analyses will be completed using Microsoft Excel and the Statistical Package for the Social Sciences (v23; SPSS Inc., Chicago IL). Before any statistical tests are performed, data will be analyzed for normality, skewness, and kurtosis. All non-normal data will be log-transformed prior to analysis. For all statistical tests, data will be considered statistically significant when the probability of a type I error is 0.05 or less. Primary endpoints for this investigation will be considered to be the delta (Week 10 – Week 2) value for DEXA fat-free mass and leg press 1RM. Secondary endpoints will be delta (Week 10 – Week 2) values for DEXA fat, DEXA lean and DEXA % fat along with bench press 1RM, bench press repetitions to fatigue, leg press repetitions to fatigue, leg press volume, peak anaerobic power, mean anaerobic power, and rate of fatigue. 2 x 2 mixed factorial (group x time) ANOVA with repeated measures on time will be used to determine any statistically significant differences for time and group main effects and group x time interaction effects. Additionally, 95% confidence intervals will be constructed of the observed changes for each group to assess within and between-group changes. All data will be presented as means  $\pm$  standard deviations.

\*required

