### Experimental Design

The study will be conducted using a randomized, double-blind approach with individuals being provided daily 2-gram doses of leucine, 2-gram doses of dileucine, or a placebo. Daily blinded supplementation will occur each day for a 10-week period of time while completing a heavy resistance training program. Dosing on workout days will occur within 60 minutes of completing each workout while doses on non-workout days will be ingested with their morning meal. On workout days, assigned dosing will be ingested within 60 minutes of completing their workout and on-days when study participants complete a workout at university facilities, the assigned supplement will be consumed in front of a research team member. The resistance training protocol will follow a linear periodization, split-body resistance training design consisting of two upper body and two lower body workouts each week resulting in each muscle group being trained twice each week. To minimize the influence of training experience and any learning effect, individuals with at least 12 months of resistance training history will be recruited. Participants follow the resistance training program for a total of 10 weeks. To assess the efficacy of the two different forms of amino acid supplementation on resistance training adaptations, changes in fat-free, lean, and fat mass will be determined using a 4-compartment body composition model. Skeletal muscle cross-sectional area will be assessed using ultrasound. Maximal strength will be assessed by determining one-repetition maximums (1RM) for the bench press and leg press exercises in addition to completion of an isometric mid-thigh pull. Muscular endurance will be assessed by determining the maximal number of repetitions completed using 80% of the 1RM (i.e. multiple-repetition maximum [RTF]) determined at baseline. Lower-body muscular power will be assessed using countermovement jumps and anaerobic capacity using a Wingate anaerobic capacity test. Participants will also be provided nutritional recommendations to ensure adequate energy and macronutrient consumption to facilitate positive training adaptations and eliminate any potential influence of differing dietary intakes. Participants will be required to provide weekly compliance and complete one supervised workout per week. After 2, 6, and 10 weeks of following the supplementation and resistance training regimens, participants will return to

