### Baseline Testing (Visit 2)

At least three days after Visit 1 to allow for completion of their food record, participants will return to the lab to complete their first testing session and begin following the resistance training and supplementation regimens. Participants will first have their body mass assessed before providing a urine sample and completing their body water, DEXA assessments (i.e. 4-compartment assessment), and muscle thickness via ultrasound. This scan will be done between the hours of 0600-1000 following an overnight fast and hydration levels will be standardized through the use of urine specific gravity measurements using a hand-held refractometer. Participants will be sent a hydration protocol to follow 24 hours prior to their visit to help ensure adequate hydration levels. This protocol will instruct the participants how much water they should be consuming throughout the day. Prior to testing, participants will complete the same standardized warm-up consisting of 5 minutes of light cycling, 10 body weight squats, 10 body weight walking lunges, 10 dynamic walking hamstring stretches (straight-leg march), and 10 dynamic walking quadriceps stretches. After the warm-up,

participants will complete five CMJ with their hands on their hips. One minute of rest will be observed between each CMJ. Participants will have their maximal voluntary isometric contraction (MVC) completed using an isometric mid-thigh pull. Three attempts will be made and one minute of rest will be observed between each test. Participants will then have their 1RM determined using the leg press exercise. Three minutes of rest will be provided after 1RM is determined and each participant will perform repetitions to failure using 80% of their previously determined 1RM to determine their repetitions to fatigue (RTF). An additional 3-minute break will be observed and then bench press 1RM and RTF will be completed using identical procedures as the leg press exercise. After observing a three-minute rest period after completion of the bench press RTF participants will complete a Wingate using a load that is equivalent to 7.5% of their body mass to measure anaerobic capacity (Lode Excalibur Sport, Lode, Netherlands). Participants will then complete an education session with a research team member to outline the dietary goals they are required to meet throughout this study. This study visit will take approximately 90 minutes to complete.

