#### Resistance Training & Supplementation Phase (Visits 3 and 4)

After completing two weeks of resistance training (8 total workouts), participants will return to the lab at a similar time (0600 – 1000 hours) for completion of an identical bout of testing. Prior to this visit, participants will complete another three-day food record and discuss with research team members about their compliance to the diet program. Participants will also have their body mass recorded. Participants will then donate a urine sample to assess hydration before completing a body water, DEXA, and ultrasound assessment. Using identical procedures as before, participants will have their CMJ performance, maximal strength (1RM and isometric mid-thigh pull) and endurance (maximal repetitions at 80% 1RM [RTF]) assessed before completing a Wingate anaerobic capacity test (WanT). New 1RM values will be used to re-assign loads during the following resistance training period. This visit will take approximately 90 minutes to complete.

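### The primary change is measured from Week 2, which the detailed schedule makes an on-treatment visit, while other sections imply supplementation starts only then; start of supplementation and endpoint window must be reconciled

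*Protocol*

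**What the plan says.** **Endpoint window.** The Statistical Analysis section defines the primary endpoints as "the delta (Week 10 – Week 2) value for DEXA fat-free mass and leg press 1RM". It continues: "Secondary endpoints will be delta (Week 10 – Week 2) values for DEXA fat, DEXA lean and DEXA % fat along with bench press 1RM", followed by the repetition, volume and Wingate outcomes.

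**Schedule in the procedures.** Experimental Design states: "Daily blinded supplementation will occur each day for a 10-week period of time while completing a heavy resistance training program". At Visit 2, which is titled as baseline testing and labelled Week 0 in Table 1, participants "complete their first testing session and begin following the resistance training and supplementation regimens". Later testing is placed on regimen: "After 2, 6, and 10 weeks of following the supplementation and resistance training regimens, participants will return to" the laboratory. The section on Visits 3 and 4 adds: "After completing two weeks of resistance training (8 total workouts), participants will return to the lab". The Final Study Visit section counts 40 workouts over about ten weeks. The text after Baseline Testing matches participants on Visit 2 fat-free mass when they are allocated. The research question (Question 13) asks about a ten-week period.

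**Text that points elsewhere.** Both Specific Aims speak of changes "after eight weeks of supplementation and heavy resistance training". The Supplementation Protocol places random assignment after participants have followed the diet and training programme. The exclusion criteria (Question 25) judge weight stability between week 0 and week 2, whereas the Body Mass section judges it between Visits 1 and 2.

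**The concern.** A change score used to compare randomised arms should normally start from a value that treatment cannot have affected. On the schedule in the procedures, Week 2 is not such a value: each participant has by then had two weeks of the assigned product and eight workouts. If one arm gains more in those two weeks, the gain raises its reference value and drops out of the contrast. The analysis then addresses what accrues between Weeks 2 and 10, while the research question concerns the whole ten weeks.

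On the other schedule implied by the aims, Week 2 would be the last pre-supplement visit and the window would be right. As the document stands, a reader cannot tell whether the primary endpoint measures the full effect or only its later part. If the reference visit were settled after data had been seen, that would be a data-driven choice of primary endpoint.

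**Working it through.** The protocol states no power, SD or expected effect, so there is no figure of its own to reproduce. The check is first of timing, then an illustration of size.

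**1. Exposure before the reference visit, on the procedures' schedule**
- Supplement weeks: 2/10 = 20%.
- Workouts: 8/40 = 20%.

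**2. The two designs side by side**

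| Element | Supplement from Week 0 | Supplement from Week 2 (run-in) |
|---|---|---|
| Research question; Question 14; Experimental Design | ten weeks: fits | does not fit |
| Baseline Testing (Visit 2) | both regimens begin: fits | does not fit |
| Allocation matched on Visit 2 fat-free mass | fits | possible |
| Week 2 testing after two weeks of both regimens | fits | does not fit |
| Specific Aims, eight weeks of supplement | does not fit | fits |
| Supplementation Protocol, assignment after diet and training | does not fit | fits |
| Exclusion criterion, weight stability Week 0 to Week 2 | does not fit | fits |
| Week 10 minus Week 2 change | omits two treated weeks | coherent |

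Table 1 cannot settle the matter: its supplementation bar is a figure that is not shown. Table 1 marks randomisation at the pre-study visit, although matching needs Visit 2 data.

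**3. What is lost**

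Let Δ be the between-arm effect at Week 10 measured from Week 0, and f the share of it present by Week 2 and persisting. The Week 10 minus Week 2 contrast then estimates (1 − f)Δ. With the SD of change held equal, the sample size for given power is multiplied by 1/(1 − f)². At f = 0.2 this is 1/0.64 = 1.56.

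**4. Illustrative power**

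Inputs from the protocol: 12 per arm, significance level 0.05. Assumptions: two-sided test, two-arm t-test, equal SD of both change scores, and the effect size and f shown. Noncentrality = d(1 − f)√(12/2), with 22 degrees of freedom. Power of 80% at f = 0 requires d = 1.197.

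| f | d(1 − f) | Power | Power if d = 1.0 at f = 0 |
|---|---|---|---|
| 0 | 1.197 | 80% | 65% |
| 0.1 | 1.077 | 71% | 56% |
| 0.2 (linear build-up) | 0.957 | 61% | 47% |
| 0.3 | 0.838 | 50% | 37% |
| 0.5 | 0.598 | 29% | 22% |

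**5. Sensitivity to the equal-SD assumption**

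With equal SDs at each visit, the SD of change is proportional to √(1 − r), where r is the correlation between the two visits. Suppose r = 0.90 over ten weeks (assumed).
- If r = 0.92 over eight weeks, the SD ratio is √(0.08/0.10) = 0.894. At f = 0.2 the standardised effect is 0.957/0.894 = 1.070, and power is 71% instead of 61%.
- If r = 0.936, the ratio is √(0.064/0.10) = 0.80, which cancels the 20% loss exactly, and power stays at 80%.

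**The case against.** **The run-in reading.** The strongest defence is that supplementation was meant to start at Week 2. The aims, the Supplementation Protocol, the weight-stability criterion and the endpoint window itself all fit that. This stands as far as it goes: one cannot simply call the window an error and everything agreeing with it residue. It does not rescue the plan, because the procedures say the opposite in several places, and the document needs correcting on either reading.

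**Learning effects.** Week 2 might be defended as a familiarised reference. The protocol gives no such rationale. It addresses learning by requiring 12 months of training history, and Visit 1 already includes the 1RM, mid-thigh pull, jump and Wingate tests. The defence keeps some force for repetitions to fatigue, which are not tested at Visit 1.

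**Stronger readings that the documents do not support.** A reader might infer any of the following.
- *The contrast is always biased toward zero.* Attenuation needs an arm difference by Week 2 in the same direction as the later one, and no early response is documented. With no supplement effect in either period, this choice does not inflate the type I error.
- *Every endpoint is affected.* The window is stated only for the outcomes listed under Statistical Analysis. The mid-thigh pull, body water, muscle cross-sectional area and rate of force development appear in the endpoint list without a defined change there.
- *The Week 0 data go unused.* Visit 2 fat-free mass drives the matching, and Visit 2 1RM sets the later endurance loads. What is true is that Week 0 does not enter the stated changes.

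**Conclusion.** The point holds. On the schedule that the procedures describe, the primary and listed secondary changes start from an on-treatment, post-randomisation visit and leave out 2 of the 10 weeks that the trial asks about. The cause is an unreconciled contradiction between a ten-week supplementation design and an eight-week one with a run-in. The text alone shows both, without any assumption.

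The size of the loss is not known. A fall from 80% to 61% power illustrates linear build-up with equal SDs of change; the range over f from 0.1 to 0.5 is 71% to 29%. These figures rest on an assumed effect, time course and SD, and on a two-arm t-test in place of the planned mixed ANOVA. A modestly higher correlation over the shorter interval could offset much or all of a 20% loss. They therefore should not be quoted as the power of this trial. Although the study is a self-described pilot, the matter should be settled before any data are seen, because it defines the primary endpoint.

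**What to change.** 1. Reconcile the Specific Aims, Statistical Analysis, Supplementation Protocol and the weight-stability exclusion criterion with the research question, Question 14, Experimental Design and the Visit 2 to Visit 5 sections, so that all give the same start and length of supplementation. Which schedule was intended is for the investigators to state.
2. In Statistical Analysis, define the primary and secondary changes from the last assessment before supplementation to Week 10. Under the schedule in the procedures that assessment is Week 0 (Visit 2), and Weeks 2 and 6 become intermediate visits.
3. Preferably include that pre-supplement value as a covariate. This is a refinement and is not needed to cure the defect.
4. Under the procedures' schedule, Week 10 minus Week 2 may be kept as a supportive analysis.

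Cost: protocol wording only. Body composition and 1RM testing are already scheduled at both Week 0 and Week 2, so neither resolution needs an added visit or measurement.

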In a randomized, double-blind, placebo-controlled fashion, participants will be matched according to their Visit 2 fat-free mass to ingest either two grams of dileucine, two grams of leucine, or a placebo (rice flour). All supplements will be provided by Ingenious Ingredients, L.P. (Lewisville, TX). On days where research participants will complete the exercise program, they will be required to consume their daily dose within 60 minutes of completing their workout. When the workout is completed at our facility, supplement ingestion will be monitored by a research team member. On non-training days, participants will consume their assigned dose with their morning meal. Participants will be given enough supplement for one week at a time as participants will be required to schedule and complete one workout per week under the direct supervision of a research team member. During these weekly workouts and check-in visits, participants will get more supplement, discuss their dietary compliance and ensure completion of their workout cards. Participants will continue to follow the prescribed resistance training program for the entire 10 weeks of the study protocol.

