### What are the characteristics of your research population?

---

23. *These could include gender, age, ethnicity, race, health status, employment status, etc? If you are recruiting multiple populations, describe by population with anticipated enrollment by population.*

Approximately 36 healthy, resistance trained males between the ages of 18-35 are proposed to complete this study.

\*required

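### The only named test has a two-level group factor, but the trial has three arms, so no single 2 x 2 analysis serves both aims

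*Protocol*

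**What the plan says.** Under Statistical Analysis, the protocol names one hypothesis test: "2 x 2 mixed factorial (group x time) ANOVA with repeated measures on time will be used". It applies a 0.05 threshold to every test. It also plans 95% confidence intervals for the change in each group, for use in within- and between-group assessment. The primary endpoints there are Week 10 minus Week 2 changes.

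Under Independent Variable there are three levels: "2 grams Dileucine (n=12)", "2 grams Leucine (n=12)" and placebo, also with 12. The total agrees with the population section: "Approximately 36 healthy, resistance trained males between the ages of 18-35 are proposed to complete this study".

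There are two Specific Aims. The first reads "In comparison to daily leucine supplementation, we aim to examine the impact of dileucine on the observed changes". The second reads "In comparison to placebo supplementation, we aim to examine the impact of leucine and dileucine on the observed changes".

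Experimental Design places the follow-up tests as follows: "After 2, 6, and 10 weeks of following the supplementation and resistance training regimens". With the Week 0 visit this makes four assessments. On allocation, the Baseline Testing section says "participants will be matched according to their Visit 2 fat-free mass".

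**The concern.** The first figure in 2 x 2 is the number of groups, and the design has three. The protocol does not say which two groups are meant, whether arms are pooled, or whether the test is repeated by pair. This goes beyond a detail left for a statistical analysis plan, because the protocol fixes the dimensions of the test and they conflict with its own design.

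Two things are at stake. Some ways of forcing three arms into two levels remove a comparison that an aim requires. And the choice of pooling or pairing stays open until the data have been seen, with nothing to control the error rate if several pairs are tested.

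**Working it through.** **Inputs.** Three arms of 12 (Independent Variable); alpha 0.05 per test (Statistical Analysis), taken here as two-sided because the protocol does not say; two time points in the endpoint (Statistical Analysis); four assessments at Weeks 0, 2, 6 and 10 (Experimental Design and Table 1). The protocol gives no power, effect size or standard deviation, so there is no sample-size figure to reproduce. The total does reproduce: 3 × 12 = 36.

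**Step 1: what each reading of a 2 x 2 does to the aims.**

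| Reading | Men used | Aim 1 (dileucine vs leucine) | Aim 2 (each vs placebo) |
|---|---|---|---|
| Pool leucine and dileucine | 36 | lost | only as a pooled comparison |
| Drop placebo | 24 | kept | lost |
| Drop leucine, or drop dileucine | 24 | lost | half kept |
| Repeat for all three pairs | 24 each time | kept | kept, with three tests |

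No single 2 x 2 serves both aims. The last row does, but the protocol does not state it.

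**Step 2: degrees of freedom.** With g groups, t times and N men, the interaction has (g − 1)(t − 1) and (N − g)(t − 1) degrees of freedom.
- 2 x 2 on one pair, N = 24: 1 and 22.
- 2 x 2 with two arms pooled, N = 36: 1 and 34.
- 3 x 2, N = 36: 2 and 33.
- 3 x 4, N = 36: 6 and 99, before any sphericity correction.

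**Step 3: error rate if the 2 x 2 is repeated by pair.** With two time points, the interaction F for two arms is the square of the t-test on the change, so the question reduces to three pairwise t-tests at 0.05.
- If the tests were independent: 1 − 0.95³ = 0.143. They are not, because each pair shares an arm with the others.
- Simulation of normal data with no true difference, 12 per arm: about 0.12 for at least one rejection.
- Omnibus three-arm F at 0.05, same simulation: about 0.05.

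**Step 4: does a three-arm model alone lower that rate?** No. Three unadjusted contrasts from one model with 33 error degrees of freedom use a critical t of 2.035. The chance that at least one exceeds it is the studentized range tail for three means beyond 2.035 × √2, which is 0.120. The rate comes down only with a rule. If contrasts are tested only after a significant omnibus test, then with no true differences the omnibus test caps the rate at about 5%. If exactly one arm differs, only one true-null pair is left, and it is tested at 0.05. With three groups these two cases cover every way in which a null hypothesis can be true.

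**The case against.** The strongest reply is that this is a slip of one digit in a trial that calls itself a pilot. A 2 x 2 on two arms is exactly the comparison in Aim 1, and two more such runs would cover Aim 2. The protocol also plans confidence intervals that bear on between-group change. Much of this stands: repeated pairwise runs could address the aims, so it would be too strong to say that the stated method can test neither. But the protocol does not state that route, and the intervals are described for each group's change, with no between-arm contrast named. Which arms enter the test is therefore still undefined.

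A reader might infer further faults that the document does not support.
- **Four assessments make the second 2 wrong.** They do not. Two time levels match the Week 10 minus Week 2 change. Leaving out Weeks 0 and 6 is a choice of endpoint.
- **Moving to three arms cuts the error rate from 12% to 5%.** Not by itself: Step 4 shows 12.0% for unadjusted contrasts.
- **Losing 12 men from each pairwise run seriously harms the test.** On critical values the effect is small: 2.074 at 22 degrees of freedom against 2.035 at 33, a difference of 1.9%.
- **Matching on fat-free mass without adjusting for it is an error.** An analysis of change is valid under randomisation. Adjustment is an improvement in precision, and covariates may properly be left to a statistical analysis plan.

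**Conclusion.** The point holds for the group factor. The one named test has two group levels, the trial has three arms, and the two aims need all three kept distinct. If the gap is filled by three unadjusted pairwise tests, the chance of at least one false positive is about 12% per endpoint. That figure assumes normal changes with equal variance, 12 men analysed per arm, two-sided tests and no true differences. It also assumes that the analyst takes the pairwise route, which the protocol neither states nor excludes. The contradiction itself rests on no assumption: Statistical Analysis must be reconciled with Independent Variable and Specific Aims before the data are analysed.

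**What to change.** Replace the 2 x 2 sentence with one three-arm model per endpoint. For the stated Week 10 minus Week 2 change this is a 3 x 2 mixed ANOVA, interaction df 2 and 33. Name the contrasts in change: dileucine minus leucine for Aim 1; dileucine minus placebo and leucine minus placebo for Aim 2. Test them only if the omnibus interaction is significant at 0.05, or use an equivalent adjustment for three comparisons. This is one paragraph of wording and needs no new data or software.

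An optional improvement is to fit the model as an ANCOVA of the Week 10 value on the three-level arm and the endpoint's pre-supplementation (Week 0) value, with the three-arm test of arm as the omnibus test. Add Visit 2 fat-free mass only for endpoints other than fat-free mass. Visit 2 is Week 0, so for fat-free mass the two covariates would be the same variable. This version replaces the Week 2 reference with Week 0, which changes the question asked, and the protocol should say so openly.

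The cost is one or two degrees of freedom: 36 − 3 − 1 = 32 or 36 − 3 − 2 = 31 for error. Against a change from Week 0, with equal variances and a Week 0 to Week 10 correlation r, the variance is multiplied by (1 + r)/2. The reduction is 5% at r = 0.9, 10% at 0.8 and 25% at 0.5. These correlations are assumed; the protocol gives none.
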